#### Blinding

The cluster representatives will know their allocated arm after random allocation, and the study procedure of only their allocated arm will be explained to them. Individual participants will be given information pertaining to the study group in their allocated cluster only after enrollment, and thus blinded. The nature of the study does not allow double blinding. However, the cluster randomized trial design will prevent contamination between the two arms of the study.

### Intervention

The two major components of the education program are the visualization tools and the special health education classes organized by the dietician. We hypothesized that after seeing both the amount of their daily dietary salt intake and the salt content in their daily food, people might be inspired to reduce dietary salt intake. Therefore, we will use visualization tools to inform the patients of their estimated 24-hour salt intake (Table
2).

**Table 2 T2:** Visualization tools used in the intervention arm of the study

**Visible salt level measurements that participants can see**	**Equipment**	**Frequency of application**	
1. Salt intake in the last 24 hours	Measurement of sodium in overnight collected urine by KME-03	Every monthly visit to the health center	
2. Dietary salt content in daily food/ soup	Pocket Salt-meter PAL-ES2 Atago, Tokyo	On the 1- and 6-month visit	

### Visualizing salt content of food by digital hand-held “pocket” salt meter

Participants will be requested to bring their usual food (e.g., curries, soup and fried foods) to the health center. We will use the digital hand-held pocket PAL-ES2 salt meter (Atago Co., Ltd, Tokyo, Japan) to measure the salt concentrations in the participants’ food (Figure
3). The salt content will be shown in displayed units of g/100 ml
[22]. This intervention informs the patients about the amount of salt in their food.

**Figure 3 F3:**
[figure not shown]
** Digital hand-held salt meter for measuring food salt content**[22].

#### Revealing estimated daily salt intake

A KME-03 salinity checker (KOUNO ME Institute, Kanagawaken, Japan) will be used to determine the estimated daily salt intake
[23]. During each monthly health center visit, participants in the intervention group will be informed of their 24-hour estimated salt intake tested from overnight collected urine. The monthly serial measurement of individual participants will be reported using an in-line graph documenting whether the salt intake is above or below 6 g /day.

#### Health education class

The small group education class will meet two times: the first, 1 month after enrollment and the second, 3 months after enrollment. The participants will be requested to bring their daily food to the health centers. The salt content in the home-made food such as soups, curries and sauces will be analyzed by a PAL-ES2 digital hand-held salt meter. The salt content in the processed food such as canned food, ready-to-eat food and instant noodles will be explained referring to the nutritional facts labels. The dangers related to a high-salt diet such as potential cardiovascular death, will be explained. There will be a taste test for participants to determine the saltiness of the sample food so that they can be made aware that individual tastes are subjectively different. After that, the dietician will explain how to reduce the daily dietary salt content based on the recommendations published by the Thailand Ministry of Public Health. These recommendations aim to reduce daily salt intake to less than 2,400 mg of sodium/day
[24].

The group education by a dietician will take 2 hours. The education will focus on continuously motivating the participants by serial assessment results and providing assistance to reduce daily dietary salt intake. The dietician will identify the traditional high-salt foods such as fish sauce, processed pork, and other products, giving advice for alternative ways of cooking palatable food without high salt levels. Dietary sodium fact sheets will be provided for the patients to keep at home.

### Control group

Participants in the control arm will receive both routine health care services and health education programs. The measurement and assessment tests will also be provided to the participants in the control arm (Table
1). Participants in the control arm will receive routine health education, which is a brief individual education session not particularly focused on salt reduction. The differences between the two arms are (1) hypothesis-driven health educational interventions and (2) revealing of the results of the serial assessment tests, such as KME −03, to the control arm participants only at the end of the trial (Table
2).

### Definition

1 Salt Reduction

Salt reduction is defined as decreasing individual salt intake to less than 6 g/day, according to the Thailand Ministry of Public Health.

2 Diabetes

Diabetes mellitus is defined as either one of the following criteria: HbA1c concentration of more than 6.5% or fasting blood glucose of more than 126 mg/dl at least twice or an on the spot blood glucose level of more than 200 mg/dl at least once, simultaneously with 2-h post-prandial blood glucose of more than 200 mg/dl or history of taking oral hypoglycemic drugs
[25,26].

3 Hypertension

Hypertension is defined as a systolic blood pressure (SBP) of ≥ 140 mmHg or a diastolic blood pressure (DBP) of ≥ 90 mmHg and higher in subjects who are not taking antihypertensive medication or subjects who are taking the medication for hypertension
[27].

4 Cardiovascular diseases (CVD) events

Myocardial infarction, coronary insufficiency, unstable angina, ischemic stroke, hemorrhagic stroke, transient ischemic attack (TIA), peripheral artery disease or heart failure will be counted as CVD events in this study. Patients with a known diagnosis of CVD will be screened and excluded.

5 CVD mortality

This is defined as any documented death caused by CVD during the study period.

### Study outcome and outcome measurements

#### Primary outcome

Blood pressure measurements will be used as the primary outcome of the study. Blood pressure will be measured serially at baseline and on the 3-, 6- and 12-month follow-up visits of the trial (Table
3). It will assess the impact of salt reduction on cardiovascular health. The HEM-907 IntelliSense professional digital blood pressure monitor (Omron Healthcare Inc., Lake Forest, IL, USA) will be used to measure blood pressure (Table
3).

**Table 3 T3:** Study outcome, outcome measurement and assessment methods

**Outcome**	**Assessment**	**Outcome measure**
Primary	Blood pressure	Omron HEM-907 IntelliSense professional digital blood pressure monitor
Secondary	Individual salt intake estimate/24-hour	Overnight urine collection and measurement of urine sodium using the KME-03 (average of 3 successive days’ measurements)
Clinical	CVD risk	General Framingham score 10-year risk
	CVD incidence	Diagnosis of each CVD event and CVD death
	Surrogate outcome	Retinal vessel caliber

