**Methods/Design:**

This is a cluster randomized trial. A total of 800 high-CVD-risk patients attending diabetes and hypertension clinics at health centers in Muang District, Chiang Rai province, Thailand, will be studied with informed consent. A health center recruiting 100 participants is a cluster, the unit of randomization. Eight clusters will be randomized into intervention and control arms and followed up for 1 year. Within the intervention clusters the following will be undertaken: (1) salt content in the daily diet will be measured and shown to study participants; (2) 24-hour salt intake will be estimated in overnight-collected urine and the results shown to the participants; (3) a dietician will assist small group health education classes in cooking meals with less salt. The primary outcome is blood pressure change at the 1-year follow-up. Secondary outcomes at the 1-year follow-up are estimated 24-hoursalt intake, incidence of CVD events and CVD death. The intention-to-treat analysis will be followed.

Blood pressure and estimated 24-hour salt intake will be compared between intervention and control groups at the cluster and individual level at the 1-year follow-up. Clinical CVD events and deaths will be analyzed by time-event analysis. Retinal blood vessel calibers of CVD-risk patients will be assessed cross-sectionally. Behavioral change to reduce salt intake and the influencing factors will be determined by structured equation model (SEM). Multilevel regression analyses will be applied. Finally, the cost effectiveness of the intervention will be analyzed.

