## Methods/Design

### Study objectives

The primary objective is to compare the effectiveness of health education via visualization of salt content in food, soup and urine, with routine health education by means of measuring blood pressure changes in high-CVD-risk patients at 1-year follow-up.

The secondary objectives are: to compare the effectiveness of specially designed health education with routine health education by means of monitoring estimated daily salt intake using urine sodium measurement, CVD incidence and retinal vessel caliber changes among diabetic and hypertension patients with high CVD risk. We will also compare the cost-effectiveness of health education via visualization of salt content in food, soup and urine with routine health education among diabetic and hypertensive patients with high CVD risk.

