### Sample size

For a conventional randomized control trial, a total of 240 participants, randomizing 120 into each arm, will have enough power (90%) to detect the minimal difference of systolic blood pressure 130 (±20) and 120 (±20) mmHg, diastolic pressure 90 (±20) and 80 (±20) mmHg, difference in 24-hour estimated salt intake 10 (±5) and 8 (±4) g/day and CVD event rate of 0.15% and 0.08% between the control and intervention group with a 95% confidence interval
[6,31]. The cluster randomized trial design used in RESIP-CVD might result in loss of power and reduced efficiency. In this cluster randomized trial, the number of participants in each cluster will be the same, and other variable factors such as geography, food tradition, race and dietary habits are assumed not to be different for delineating the intracluster coefficient. To compensate the design effect, the inflation factor has been calculated by the formula (*Deff* = 1 + (*m–1*)*ρ*) where *Deff* is inflation factor for design effect, *m* is the size of each cluster, which is 30 and *ρ* is the intracluster coefficient which is assumed to be 0.07. The sample required for a cluster randomized trial was inflated to 720. With a loss to follow-up of approximately 10%, we expect that the sample size of 800 patients will yield sufficient power to detect the desired minimal difference in primary and secondary outcomes between the intervention and control group. All eight clusters of the RESIP-CVD study will enroll 100 eligible participants.

We identified the confounders and planned to collect the information for multivariate analysis adjustment. (Table
4)

**Table 4 T4:** Confounder measurements

**Confounder**	**Variables**	**How to measure**
Demographic characteristics	Age, sex, social status, family size, educational attainment, occupational history, income	Questionnaire
Lifestyle	Smoking, alcohol	Questionnaire
Genetic factor	Family history of diabetes/hypertension	Questionnaire
Drugs	Different medications for diabetes and hypertension	Clinical record

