### Analysis plan

The intention-to-treat analysis will be followed. The mean blood pressure and mean daily salt intake of both the intervention and control arms will be compared at the individual level at the 1-year follow-up using Student’s *t* test or the non-parametric test based on distribution. The analysis will be carried out at both the cluster and individual levels. The CVD incidence rate will be compared by time-to-event analysis. A structural equation modeling analysis will be used to determine the behavioral change predictors. Information such as the self-efficacy, stage of attitudinal change, decisional balance, family support, health center support, ready-made meals usage and cooking utensils will be collected by questionnaires and analyzed by the SEM (Figure
4).

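### The protocol does not say whether systolic, diastolic, either or both pressures decide the primary outcome; if either suffices, false-positive risk reaches up to 9.75% even with a valid clustered test

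*Protocol article*

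**What the plan says.** Each statement of the primary outcome stops at blood pressure. The abstract (Methods/Design) says "The primary outcome is blood pressure change at the 1-year follow-up". Study objectives frames the primary objective as "measuring blood pressure changes in high-CVD-risk patients at 1-year follow-up". The Primary outcome section says "Blood pressure measurements will be used as the primary outcome of the study", and Table 3 adds only the measuring device. The Analysis plan compares mean blood pressure between arms at one year with an individual-level Student's t test or a non-parametric test, then adds "The analysis will be carried out at both the cluster and individual levels".

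Only the Sample size section separates the components. It claims "enough power (90%) to detect the minimal difference of systolic blood pressure 130 (±20) and 120 (±20) mmHg" and, in the same sentence, "diastolic pressure 90 (±20) and 80 (±20) mmHg". That sentence also sizes salt intake and CVD events. Its mention of a 95% confidence interval is the protocol's only statement about error rate.

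The one-year time point is fixed by the abstract, the objective and the Analysis plan, and is not in question here.

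**The concern.** One outcome label covers two separately sized variables, with no ranking, no success rule and no shared alpha. At the end of the trial there will be two blood pressure comparisons. If one is significant and the other is not, the protocol does not say whether the primary objective was met.

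Two things are at stake. First, the reading of a mixed result could be chosen after the data are seen. Second, if that reading lets either component carry the claim, the primary conclusion no longer has the 5% error rate that a 95% confidence level suggests. Naming the deciding variable is the protocol's own task, so this goes beyond detail that a statistical analysis plan would normally supply.

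**Working it through.** **Inputs from the protocol.** Systolic 130 v 120 mmHg and diastolic 90 v 80 mmHg, SD 20 each, 90% power, 120 per arm before clustering, cluster size 30 and intracluster coefficient 0.07 in the design effect (all Sample size); 100 participants per cluster and four clusters per arm (Study site). A 95% confidence interval is read as two-sided 5% per comparison. **Assumed:** the correlation between the systolic and diastolic test statistics, which is not given.

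**Step 1, the plan's own figure.** n per arm = 2 × SD² × (1.960 + 1.2816)² / difference² = 2 × 400 × 10.507 / 100 = 84.06, so 85. The stated 120 per arm gives 97.2% power for either pressure, so 240 is not reproduced by the stated inputs. The later steps do follow: 240 × (1 + 29 × 0.07) = 240 × 3.03 = 727, close to 720, and 720 / 0.9 = 800. None of this changes the present point.

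**Step 2, error if either component suffices and each test is valid at 5%.** With Z1 and Z2 the two test statistics, the risk is 1 − P(|Z1| ≤ 1.96 and |Z2| ≤ 1.96). At zero correlation this is 1 − 0.95² = 9.75%, the upper limit for bivariate normal statistics. The third column is a simulation of 400,000 trials with four v four cluster means and a t test on 6 df; each single test there ran at about 5.0%.

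| Assumed correlation | Normal theory | Cluster-level t test, simulated |
|---|---|---|
| 0 | 9.75% | 9.77% |
| 0.5 | 9.07% | 9.27% |
| 0.6 | 8.75% | 9.10% |
| 0.7 | 8.35% | 8.66% |
| 0.75 | 8.10% | not run |
| 0.8 | 7.81% | 8.14% |
| 0.9 | 7.04% | not run |
| 1 | 5% | not run |

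These figures count false positives in both directions. Counting only results that favour the intervention (2.5% per test), normal theory gives 4.94% at correlation 0, 4.54% at 0.5 and 4.05% at 0.75.

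**Step 3, other success rules.** One named component: 5%. Both required: at most 5%. Alpha split at 0.025 each: at most 5%. The required n under a split becomes 100 per arm before clustering, still below the stated 120.

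**Step 4, does the 5% baseline hold?** Not for an individual-level t test that ignores clustering. With the protocol's coefficient and 100 per cluster, the design effect is 1 + 99 × 0.07 = 7.93. The real size of a nominal 5% test is then 2 × [1 − Φ(1.96 / √7.93)] = about 49% for one component alone. Accepting either component would give about 66-71% at correlations of 0.75 to 0.5. With 90 per cluster after 10% loss, the design effect is 7.23 and the single-test figure is 46.6%. The table in Step 2 therefore applies only to an analysis that respects clustering.

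**The case against.** The protocol nowhere says that either component alone is enough. If the investigators mean both to be required, nothing is inflated. This stands, so the inflation can be stated only conditionally. The undefined reading of a mixed result remains.

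A reader might infer from the Sample size section that the trial has two primary variables. The text does not support that: the same sentence sizes salt intake ("difference in 24-hour estimated salt intake 10 (±5) and 8 (±4) g/day") and CVD events, which the protocol lists as secondary. Being sized there does not make a variable primary. What stands is that the two pressures are the only candidates under the primary label and neither is chosen.

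Testing order, alpha sharing and the choice between analysis levels are commonly left to a statistical analysis plan, and a condensed article may omit them. That is fair, and their absence alone would be no finding. The identity of the primary variable is different, because the article addresses it in several places without settling it.

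Finally, preferring systolic pressure is a judgement. Its use in the Framingham score (Baseline survey) explains eligibility, and does not by itself show that it should decide effectiveness. This also stands, so systolic is offered only as a reasonable choice.

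**Conclusion.** The point holds as an ambiguity with a conditional cost. The protocol does not say whether systolic, diastolic, either or both pressures decide the trial. If either suffices, the two-sided false-positive risk is up to 9.75%, and about 8-9% for an assumed correlation of 0.5-0.75. If both are required, it is at most 5%.

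A reader might conclude that the trial as written runs at 8-9% instead of 5%. The documents do not support that, for three reasons: they state no either-one rule, they give no correlation, and the individual-level t test in the Analysis plan would not hold 5% even for a single component (about 49% at the protocol's own coefficient). The abstract mentions multilevel regression and the Analysis plan a cluster-level analysis, but neither is named as deciding. The 8-9% figure belongs to such an analysis only. The change should be made, and before outcome data are examined, since Trial status reports that recruitment is under way.

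**What to change.** State in the Primary outcome and Analysis plan sections which variable decides the trial, choosing one of these:

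- **Fixed order.** Name one component at 12 months as the single primary variable; systolic is a reasonable choice. Test the other at 5% only if the first is significant. This costs no power for the first variable, but an effect on the second alone could no longer be claimed as a primary result.
- **Both required.** Declare that both must be significant at 5%. The error stays at or below 5%, but power for joint success is lower than for either alone, and an effect on one pressure only does not count.
- **Alpha split.** Test each at 0.025, with success on either. The individually randomised requirement rises from 85 to 100 per arm before clustering, within the stated 120.

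In the same place, name as primary an analysis that respects clustering, either cluster-level or multilevel, and state that the individual-level t test is not the deciding test. Without this, naming one component would not secure 5%. The whole change is a sentence or two and alters no visit or measurement.

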### Secondary outcome

Individual salt intake will be monitored to assess the behavioral changes related to salt intake. Overnight collected urine will estimate the salt intake by a KME-03 intake salinity checker
[28-30]. The mean value of 3 successive days’ measurements will be recorded and assessed as outcome measures at baseline and on the 3- and 12-month visits. The CVD risk assessment, CVD events and CVD-related deaths will be followed up (Table
3). The Framingham general CVD risk score will be measured at study entry and assessed again at the end of the study period to assess whether salt reduction decreases the CVD risk. CVD event diagnosis will be based on the physician’s decision by clinical and confirmatory tests for respective CVD events at regional- or district-level hospitals. CVD events will be counted whenever they are newly diagnosed among study participants. Deaths caused by CVD and confirmed by the hospital records will be counted as CVD deaths. A masked committee consisting of two physicians who do not know the participant’s study arm will confirm the CVD events. Also of note, the retinal vessels caliber measurement will be used as a surrogate outcome for a CVD risk assessment.

### Sample size

For a conventional randomized control trial, a total of 240 participants, randomizing 120 into each arm, will have enough power (90%) to detect the minimal difference of systolic blood pressure 130 (±20) and 120 (±20) mmHg, diastolic pressure 90 (±20) and 80 (±20) mmHg, difference in 24-hour estimated salt intake 10 (±5) and 8 (±4) g/day and CVD event rate of 0.15% and 0.08% between the control and intervention group with a 95% confidence interval
[6,31]. The cluster randomized trial design used in RESIP-CVD might result in loss of power and reduced efficiency. In this cluster randomized trial, the number of participants in each cluster will be the same, and other variable factors such as geography, food tradition, race and dietary habits are assumed not to be different for delineating the intracluster coefficient. To compensate the design effect, the inflation factor has been calculated by the formula (*Deff* = 1 + (*m–1*)*ρ*) where *Deff* is inflation factor for design effect, *m* is the size of each cluster, which is 30 and *ρ* is the intracluster coefficient which is assumed to be 0.07. The sample required for a cluster randomized trial was inflated to 720. With a loss to follow-up of approximately 10%, we expect that the sample size of 800 patients will yield sufficient power to detect the desired minimal difference in primary and secondary outcomes between the intervention and control group. All eight clusters of the RESIP-CVD study will enroll 100 eligible participants.

We identified the confounders and planned to collect the information for multivariate analysis adjustment. (Table
4)

**Table 4 T4:** Confounder measurements

**Confounder**	**Variables**	**How to measure**
Demographic characteristics	Age, sex, social status, family size, educational attainment, occupational history, income	Questionnaire
Lifestyle	Smoking, alcohol	Questionnaire
Genetic factor	Family history of diabetes/hypertension	Questionnaire
Drugs	Different medications for diabetes and hypertension	Clinical record

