### Map of the study area

#### Study population

In this study, the study population will comprise high-CVD-risk patients stratified by the Framingham general CVD risk scoring system
[18,19]. Only those patients who have a CVD risk score higher than 15% will be included.

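### The 90% power claimed with 120 per arm does not hold for CVD events: rates of 0.15% vs 0.08% need about 49,000 per arm

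*Protocol article*

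**What the plan says.** The *Sample size* section opens with a conventional, individually randomised trial: "a total of 240 participants, randomizing 120 into each arm, will have enough power (90"%) to detect four contrasts. These are "systolic blood pressure 130 (±20) and 120 (±20) mmHg", "diastolic pressure 90 (±20) and 80 (±20) mmHg", salt intake of 10 (SD 5) against 8 (SD 4) g/day, and a "CVD event rate of 0.15% and 0.08% between the control and intervention group with a 95% confidence interval". No time unit is attached to the event rates.

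The section inflates 240 to 720 for clustering and to 800 for about 10% loss. It concludes that 800 patients give enough power "to detect the desired minimal difference in primary and secondary outcomes between the intervention and control group".

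The Abstract names the incidence of CVD events and CVD death as secondary outcomes at 1 year, and the *Secondary outcome* section describes how they are ascertained. The *Analysis plan* states: "The CVD incidence rate will be compared by time-to-event analysis". The *Discussion* says that events and deaths will be compared to establish the clinical effectiveness of the programme.

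**The concern.** One sentence attaches a single power figure to three continuous contrasts and to a difference of 0.07 percentage points between two very rare proportions. A sample that suits the first three cannot suit the fourth.

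The closing sentence of the section then extends adequate power to the secondary outcomes, which include CVD events and deaths. The *Baseline survey* section also justifies restricting entry to high-risk patients partly on the ground that a low event incidence could call for more patients than were calculated. The event outcome is therefore treated as if the calculation covered it.

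The stake is interpretation. Under a published claim of sufficient power, a null result on a handful of events could be read as no clinical effect, and a chance imbalance as benefit.

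**Working it through.** **Inputs.** From *Sample size*: 120 per arm, 90% power, the four contrasts, m = 30, intracluster coefficient 0.07, 10% loss. From the study site section: four clusters of 100 per arm, so 400 per arm. Follow-up is 1 year. Two-sided 5% is read from "with a 95% confidence interval"; sidedness is not stated. (1.960 + 1.282)² = 10.507.

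**1. The parts that reproduce.**
- SBP and DBP: n = 10.507 × 2 × 20² / 10² = 84.06, so 85 per arm. Power at 120 is 97%.
- Salt: n = 10.507 × (5² + 4²) / 2² = 107.7, so 108 per arm. Power at 120 is 93%.
- Inflation: 1 + 29 × 0.07 = 3.03; 240 × 3.03 = 727, close to the stated 720; 720 / 0.9 = 800.

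**2. CVD events: sample size needed.** n = 10.507 × [p1(1−p1) + p2(1−p2)] / (p1−p2)².
- Numerator variance: 0.00149775 + 0.00079936 = 0.00229711. Squared difference: 0.0007² = 0.00000049.
- n = 10.507 × 0.00229711 / 0.00000049 = about 49,259 per arm (49,262 with pooled variance).
- Variants: 52,080 with continuity correction; 40,150 one-sided; 107 events (Schoenfeld) or 114 (Freedman), which divided by 0.0023 give about 46,500 or 49,600 per arm.
- With the protocol's design effect: 49,262 × 3.03 = about 149,000 per arm.

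**3. CVD events: power available.** Power = Φ(0.0007 / √(0.00229711 / n) − 1.96).
- n = 120: Φ(0.160 − 1.96) = 3.6%.
- n = 400, ignoring clustering: Φ(0.292 − 1.96) = 4.8%.
- One-sided: 6.9% and 8.8%.
- The normal approximation is poor with so few events. Fisher's exact test gives essentially zero at 120 and about 0.003% at 400.

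**4. Expected events, if the rates are 1-year risks.** 400 × 0.0015 = 0.60 and 400 × 0.0008 = 0.32, total 0.92. The chance of no event is 0.9985^400 × 0.9992^400 = 0.549 × 0.726 = 0.40. With 720 completers the total is 0.83 and the chance of none is 0.44. If the rates are 10-year risks, fewer events are expected.

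**5. Could the rates be misprinted?**

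| Reading | n per arm for 90% | Power at 120 per arm | Power at 400 per arm, no clustering |
|---|---|---|---|
| 0.15% vs 0.08% | 49,259 | 3.6% | 4.8% |
| 1.5% vs 0.8% | 4,870 | 7% | 15% (8% by Fisher) |
| 15% vs 8% | 431 | 40% | 87% |

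Under the last reading, the design effect reduces 400 to 400 / 3.03 = 132 effective patients per arm, and power to about 43%. No reading gives 90% at 120 per arm.

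**6. The missing time unit.** *Study population* states: "Only those patients who have a CVD risk score higher than 15% will be included"; *Baseline survey* makes this a 10-year risk. At constant hazard, 15% over 10 years is 1 − 0.85^0.1 = 1.6% per year. Read as an annual risk, 0.15% is about one tenth of that.

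**The case against.** The primary outcome is blood pressure, and the 800 is built from 240 × about 3.03 plus 10% loss. Deleting the CVD clause alters no patient number, no primary analysis and no trial conduct. That stands.

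Three stronger readings are tempting, and the document does not support them.

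- *The event rate contradicts the entry rule.* This needs 0.15% to be annual, the hazard to be constant and the Framingham score to be calibrated in this population. None of these is stated. Read as monthly, 0.15% becomes 1 − 0.9985^12 = 1.8% per year, which fits a 10-year risk above 15%. Power at 400 per arm would still be only about 17% (normal approximation, no clustering). What remains is that the unit must be given. The figure of about one event depends on it too: at 1.6% per year and the same ratio, 400 per arm would give about 6.4 and 3.4 events.
- *The event comparison is confirmatory.* The *Analysis plan* says only that a time-to-event analysis will be done, and Table 3 lists CVD incidence under a clinical heading apart from the salt-intake row. Even so, the Abstract calls it secondary, and the power sentence covers secondary outcomes.
- *The cost-effectiveness results rest on these few events.* The economic text describes extrapolation over 10 years and a lifetime, drawing for the lifetime part on data from inside and outside Thailand. It does not say that observed trial events drive the model, so no change to that model follows from this point.

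**Conclusion.** The stated power is wrong for CVD events. By the protocol's own rates, 120 per arm falls short by a factor of about 410 (49,259 / 120) before clustering, and power at 120 or 400 per arm is below 5% two-sided. This does not depend on the time unit, on the choice among the usual formulas, or on a one-sided test. Neither plausible decimal misprint rescues the 90%.

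The figures of 0.92 expected events and a 40% chance of none are conditional: they assume the rates are cumulative risks over the 1-year follow-up with no loss.

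The error is confined to the CVD-event clause and to the sentence that carries sufficient power over to all secondary outcomes. A reader might infer that the blood pressure comparison is undermined as well. This point gives no ground for that, since 120 per arm exceeds 90% power for SBP, DBP and salt intake before clustering. Whether the clustering inflation is adequate (it uses a cluster size of 30, while each cluster enrols 100) is a separate question, not judged here.

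**What to change.** - In *Sample size*, delete the CVD event rates from the power statement. If they are kept anywhere as background, give their time unit.
- Restrict the closing sentence on primary and secondary outcomes to blood pressure and salt intake.
- In the Abstract, *Secondary outcome*, *Analysis plan* and *Discussion*, label CVD events and deaths exploratory. Report counts and rates by arm with confidence intervals, and say that neither a null nor an imbalanced result will be read as evidence on clinical effectiveness.

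The cost is wording and a weaker stated claim for CVD events. This correction changes neither the sample size of 800 nor the primary analysis, and it needs no new data.
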